## Abstract

In women at high/intermediate lifetime risk of breast cancer (BC-LTR), contrast-enhanced magnetic resonance imaging (MRI) added to mammography ± ultrasound (MX ± US) increases sensitivity but decreases specificity. Screening with MRI alone is an alternative and potentially more cost-effective strategy. Here, we describe the study protocol and the characteristics of enrolled patients for MRIB feasibility, multicenter, randomized, controlled trial, which aims to compare MRI alone versus MX+US in women at intermediate breast cancer risk (aged 40–59, with a 15–30% BC-LTR and/or extremely dense breasts). Two screening rounds per woman were planned in ten centers experienced in MRI screening, the primary endpoint being the rate of cancers detected in the 2 arms after 5 years of follow-up. From July 2013 to November 2015, 1254 women (mean age 47 years) were enrolled: 624 were assigned to MX+US and 630 to MRI. Most of them were aged below 50 (72%) and premenopausal (45%), and 52% used oral contraceptives. Among postmenopausal women, 15% had used hormone replacement therapy. Breast and/or ovarian cancer in mothers and/or sisters were reported by 37% of enrolled women, 79% had extremely dense breasts, and 41% had a 15–30% BC-LTR. The distribution of the major determinants of breast cancer risk profiles (breast density and family history of breast and ovarian cancer) of enrolled women varied across centers.

## 1. Introduction

Mammography (MX) represents the primary screening tool for breast cancer, but its preventive impact is not fully satisfactory. Considering the screening age range, MX yields an estimated breast cancer mortality reduction of about 30% in the target population, with a beneficial effect persisting for at least 10 years [1,2]. However, even for women who regularly adhere to a screening program, risk reduction brought about by MX screening remains approximately 40% [3]. Such limited efficacy has been attributed to both the intrinsic limitations of MX and the highly variable biological characteristics of breast cancer [4], as well as to women’s individual characteristics such as age and breast density (BD). A high BD is an independent breast cancer risk factor for both premenopausal and postmenopausal women [5,6], and it also reduces MX sensitivity (masking effect), resulting in an increased interval cancer rate [7,8,9]. While tomosynthesis, contrast-enhanced magnetic resonance imaging (MRI), and contrast-enhanced mammography may all display increased sensitivity, compared to MX, especially for small breast cancers [10,11,12], a more sensitive test could detect more small tumors only because they are growing slowly, potentially leading to an increase in overdiagnosis [13].

In high-risk women, the addition of MX to MRI did not substantially increase sensitivity [14,15,16,17,18]. Moreover, supplementary screening breast ultrasound (US) or MRI in addition to MX in these women resulted in a higher cancer detection rate [16,19] but also increased the false-positive rate [16,20]. In this context, any attempt to improve screening efficacy by increasing the sensitivity of the process/test(s) needs to be carefully evaluated, since it might produce more harm than benefit. Furthermore, no study has demonstrated that the addition of MRI to traditional imaging in high-risk women reduces breast cancer-related mortality. In the absence of clear evidence, there is no consistent recommendation from international guidelines on a threshold of breast cancer lifetime risk (BC-LTR) that warrants the recommendation of periodic MRI surveillance [21,22].

In two cohort studies outside the high-risk setting, focused on healthy women who underwent MRI and MX with or without US, MRI had better sensitivity than MX with or without US, particularly in women with dense breasts [11,23]. No interval cancers were observed [11], but the net benefit and additional costs of MRI were not estimated. In the DENSE trial, the supplemental MRI screening in women with extremely dense breasts and negative MX resulted in a significantly lower interval breast cancer rate than MX alone [24].

However, an add-on strategy (i.e., adding tests to MX) to increase the sensitivity of the screening process may decrease specificity and potentially increase overdiagnosis. An alternative strategy, i.e., replacing MX plus US with MRI, could be more risk- and cost effective. This hypothesis has never been explored in a classical head-to-head trial. However, a typical efficacy trial requires the recruitment of tens of thousands of subjects and would require evidence, up to now unavailable, on the acceptability and actual performance of MRI, as a stand-alone screening test among women at intermediate risk of breast cancer are not available. Thus, the MRIB feasibility multicenter, randomized, controlled trial was started in 2013 in Italy, aiming to compare the performance of contrast-enhanced MRI as a stand-alone screening tool versus MX plus US in women at intermediate breast cancer risk and investigate the feasibility of a larger efficacy trial. We here describe the study design and protocol and analyze the distribution of patients’ characteristics and breast cancer risk profiles in the enrolled cohort.

## 2. Study Design and Protocol

This study is in accordance with the ethical standards of the institutional research committees (Ethics Committee of Regione Liguria for the coordinating center and each participating center competent Ethics Committee). All women enrolled in the study received an information sheet and signed written informed consent.

### 2.1. Study Design and Population

Women were randomly assigned to receive annual 2D MX plus US (standard-of-care arm) or MRI (experimental arm) with a 1:1 allocation ratio. Two screening rounds per woman were planned.

Women were deemed eligible for enrollment if aged 40–59 years and if they had a 15–30% BC-LTR and/or extreme BD on the most recent MX. BC-LTR was calculated using the IBIS Breast Cancer Risk Evaluation Tool version 6.0.0 (http://www.ems-trials.org/riskevaluator/, accessed on 30 August 2021).

Exclusion criteria were signs or symptoms of breast cancer, previous breast cancer (invasive or ductal in situ), cancer at any other site, presence of life-threatening diseases, known *BRCA* or *TP53* pathogenic germline mutation, and pregnancy. We also excluded women with general contraindications to MRI or to intravenous administration of gadolinium-based contrast agent; women who underwent hormonal enhancement of ovarian function for medically assisted reproduction in the previous three years; women planning a pregnancy; women undergoing postmenopausal hormone replacement therapy (HRT) who refused to suspend the treatment four weeks before MRI performance.

### 2.2. Enrollment

Women aged 40–59 years who had an MX scheduled during the study period were interviewed to check their eligibility; they were concurrently informed about the study aims and the associated potential risks and benefits. Those who accepted to participate signed informed consent and were randomized. Randomization was centralized via a web-based connection to the coordinating center (http://ctrials.hsanmartino.it/ist/rde/, accessed on 30 August 2021). After eligibility had been checked, the assignment of each woman was disclosed to the center. Randomization was stratified according to center and women’s age at enrollment (<50 or ≥50 years).

### 2.3. Participating Centers and Imaging Readers

According to the EUSOMA recommendations [25], the following facilities had to be available at each participating center: (1) an electronic image storage system for MX, US, and MRI; (2) full-field digital MX systems; (3) breast US scanners; (4) MR units with magnets with field intensity ≥ 1.0 T and gradients ≥ 20 mT/m (details in Table 1). Radiologists involved in the study had to document their experience in breast imaging, i.e., the performance and/or interpretation of at least 500 breast MRI, 10,000 MX, and 5000 US examinations, adequate skill in interventional procedures (under stereotactic or US guidance), and the interpretation of at least 150 breast MRI examinations in the previous year. In addition, participating centers had to guarantee the performance of needle biopsy (core or vacuum-assisted) under stereotactic, US, and MRI guidance; second-look US and reevaluation of MX to identify MRI-detected lesions; availability of preoperative localization under stereotactic, US, and MRI guidance. In total, 10 qualified centers with long experience in breast MRI screening for high-risk women (as in the HIBCRIT study [15]) joined the study, and a team of investigators was established at each center.

### 2.4. Imaging Interpretation

Examinations were interpreted according to the BI-RADS classification system for MX, US, and MRI [26]: category 0 (non-diagnostic), category 1 (negative), category 2 (benign), category 3 (probably benign, i.e., cancer probability < 2%), category 4 (suspicious abnormality—biopsy should be considered) and category 5 (highly suggestive of malignancy—appropriate action should be taken).

Mammographic BD was visually evaluated and categorized according to the following American College of Radiology (ACR) categories: (1) almost entirely fat (*a*), (2) scattered fibroglandular densities (*b*); (3) heterogeneously dense, which may obscure small masses (*c*); (4) extremely dense, which lowers MX sensitivity (*d*) [26]. When the breasts were not of apparently equal BD, the denser one was used to categorize BD.

### 2.5. Diagnostic Workup

In both study arms, women with examinations classified as BI-RADS category 0 repeated imaging tests; those classified as BI-RADS categories 1 or 2 were returned to the assigned arm or to usual screening if the two study rounds had been completed. Women with examinations classified as BI-RADS category 4 or 5 were immediately invited to undergo further diagnostic and/or interventional procedures, as appropriate.

Women who had MX and/or US examinations classified as BI-RADS category 3 were invited to repeat MX and/or US within 6 months (early recall) according to the characteristics of the detected lesion(s). If the early recall exams were classified as BI-RADS category 1 or 2, women returned to the assigned group or to screening; if they were classified as BI-RADS category 3 to 5, the women were invited to undergo further diagnostic and interventional procedures.

Women who had MRI classified as BI-RADS category 3 were referred to second-look US and/or reevaluation of MX according to the characteristics of the observed lesion(s). Those who had the second-look/reevaluation test(s) classified as BI-RADS category 1 or 2 were returned to the assigned study arm or to screening. Women with test(s) classified as BI-RADS category 3 were invited to repeat MX and/or US after 3 months; short-term follow-up with MRI was not considered. If the result of the 3-month examination(s) remained BIRADS category 3 or worsened to category BI-RADS 4, or 5, the women were invited to undergo interventional procedures.

Diagnostic and interventional procedures performed in the workup of detected abnormalities (either after screening examination or after short-term follow-up) included fine-needle sampling, core-needle biopsy with at least 14 g bore devices with or without coaxial systems, and vacuum-assisted biopsy with at least 11 g bore devices. The diagnostic workup in the two study arms is reported in Figure 1.

### 2.6. Data Collection

The following data were collected upon enrollment of each woman: reproductive history, use of birth control pill, HRT, height, weight, alcohol consumption, tobacco smoking history, first-degree family history of breast cancer and of ovarian cancer (OC), ACR density class at the most recent MX, and BC-LTR.

The coordinating center was responsible for data storage, monitoring, and quality controls of the study, as well as for the assessment of main study endpoints. The Clinical Trials Center of the coordinating center developed the electronic case report forms to record: imaging data examinations, pathology data for lesions biopsied and/or removed, details of surgical procedures, stage of detected breast cancer, eventual adverse events. A password-protected database was designed and managed, each researcher receiving a personal login/password. The Clinical Trials Center was also in charge of monitoring data collection and auditing the filled-in case report forms. Participating centers provided de-identified data according to current regulations. At the Clinical Trials Center, the enrolled women were identified with a unique study number assigned at randomization.

### 2.7. Study Endpoints

The primary endpoint of this study was the rate of invasive and ductal in situ breast cancer detected in the two study arms. All breast cancers diagnosed as a consequence of an abnormality identified at the screening tests were considered screen detected.

Secondary endpoints included (1) the distribution of clinical and pathological stages of invasive breast cancers; (2) the histological characteristics of breast cancers; (3) the interval cancer rate, both between the two examinations and within one year from the second examination: any breast cancer (invasive or ductal in situ) diagnosed after a negative examination but before the following examination, scheduled approximately 1 year later, would be considered as an interval cancer; (4) the adherence to the assigned arm and any reason for consent withdrawal from the assigned program; (5) the distribution of the breast cancer risk profiles; (6) the number of breast cancers (invasive and in situ) detected in excess in the experimental arm compared to the conventional arm (overdiagnosis) after 4 years of follow up. The breast cancer risk profile was built combining the LTR score (<15% or ≥15%) and the BD at the most recent mammography before enrollment (ACR class *a* to *c*, or ACR class *d*), so that four risk categories (risk profile) were created: (1) LTR ≥ 15% and BD = *a* to *c*; (2) LTR < 15% and BD = *d*; (3) LTR ≥ 15% and BD = *d*; (4) LTR ≥ 15% and unknown BD.

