It can be expected that in this feasibility trial, over a 5-year screening period, about 40–60 cases of invasive breast cancer will be observed: one-third in the control arm; two-thirds in the MRI arm. These figures are close to those of previous uncontrolled MRI studies (e.g., the HIBCRIT study [15]) and would enable us to confirm the twofold increase in sensitivity associated with MRI. These figures were also considered sufficient to provide preliminary information on the MRI-associated lead time and on the stage distribution of incident breast cancers. Conversely, the number of advanced (metastatic or locally advanced) breast cancers and the number of breast-cancer-related deaths should be too small to allow any meaningful interpretation. Due to lead time, no effects of MRI on efficacy endpoints are expected to be noted during the first years. Any estimation of the proportion of interval cancers in each arm proved to be difficult, as this proportion is dependent on the age distribution of enrolled women.

Two and half years since the start of the study, when 1254 women had been randomized, enrollment stopped due to the end of the grant, and screening and diagnostic imaging was completed. A clinical follow-up of all randomized women is planned for at least 5 years.

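### The stage endpoint is a distribution among invasive cancers, so MRI could show a smaller later-stage share without any fewer later-stage cancers

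*Protocol article*

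**What the plan says.** Section 2.7 of the protocol article lists stage as secondary endpoint 1, "the distribution of clinical and pathological stages of invasive breast cancers", and histology as endpoint 2, "the histological characteristics of breast cancers". Other items in the same list take a different form: interval cancers are given as a rate, and overdiagnosis as an excess number of cancers at 4 years. No stage-specific rate per woman randomised appears.

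Section 2.8 expects that "about 40–60 cases of invasive breast cancer will be observed" over 5 years in the planned 2000 women, split "one-third in the control arm; two-thirds in the MRI arm". Randomisation is "with a 1:1 allocation ratio" (section 2.1). Section 2.8 regards these case numbers as enough for "preliminary information on the MRI-associated lead time and on the stage distribution of incident breast cancers". It also says that metastatic or locally advanced cancers and breast cancer deaths will be too few to interpret, and that lead time rules out visible efficacy effects in the first years.

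The Introduction warns that "a more sensitive test could detect more small tumors only because they are growing slowly", with possible overdiagnosis as a result. Section 2.6 lists "stage of detected breast cancer" among the case report form items.

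**The concern.** The denominator of a stage distribution is the number of invasive cancers diagnosed. That number is an outcome arising after randomisation, and the plan itself expects it to differ twofold between arms. Extra cancers found by a more sensitive test are likely to be small and slow-growing, which is the mechanism named in the Introduction. They add to the early-stage count and dilute the later-stage share, whether or not any later-stage cancer has been averted. The article acknowledges lead time and overdiagnosis but does not connect either to how the stage distribution should be read.

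At stake is interpretation. A stage table by arm, expressed as percentages of cases, can look like a favourable shift when the two randomised groups have the same burden of later-stage disease. The rate per woman randomised does not have this fault, because its denominator is fixed by randomisation.

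**Working it through.** **Inputs from the document**
- Planned enrolment: 2000 women, allocated 1:1, so about 1000 per arm (sections 2.8 and 2.1).
- Expected invasive cancers over 5 years: 40 to 60, one-third control and two-thirds MRI (section 2.8).
- Average 10-year breast cancer risk: 5% (section 2.8).
- Women randomised: 624 control, 630 MRI (section 3).

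**Input not in the document**
- The later-stage share of invasive cancers in the control arm. It is assumed here to lie between 20% and 50%.

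**Step 1: the plan's own case count.** Spreading the 10-year risk evenly, 2000 × 5% × 5/10 = 50 cancers, inside the stated 40 to 60. The figure is reproduced.

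**Step 2: the split.** With 60 cancers, control has 60 × 1/3 = 20 and MRI has 60 × 2/3 = 40. With 40 cancers the arms have 13.3 and 26.7. The ratio of cases, r, is 2 either way.

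**Step 3: share among cases when no later-stage cancer is averted.** Let a be the later-stage count, equal in both arms. The control share is a/20 and the MRI share is a/40.

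| Later-stage cancers per arm | Control share | MRI share | Rate per 1000 women, each arm |
|---|---|---|---|
| 4 | 4/20 = 20% | 4/40 = 10% | 4 |
| 6 | 6/20 = 30% | 6/40 = 15% | 6 |
| 8 | 8/20 = 40% | 8/40 = 20% | 8 |
| 10 | 10/20 = 50% | 10/40 = 25% | 10 |

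The share is halved whatever the starting value, and the rate ratio per woman is 1.0 in every row.

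**Step 4: catch-up in the control arm.** With equal later-stage counts, MRI share = control share / r. If later control-arm diagnoses bring r down to 1.5, 20% becomes 13.3% and 50% becomes 33.3%. At r = 1 the artefact is gone. Halving is therefore the size at the plan's own 2:1 expectation, and catch-up makes it smaller.

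**Step 5: at the size actually enrolled.** Scaling gives 40 × 1254/2000 = 25 to 60 × 1254/2000 = 38 cancers. The midpoint is 50 × 1254/2000 = 31, or about 10 control and 21 MRI. With an illustrative 5 later-stage cancers in each arm:
- Share among cases: 5/10 = 50% against 5/21 = 24%.
- Rate per woman randomised: 5/624 = 8.0 against 5/630 = 7.9 per 1000.
- Rate ratio: (5/630)/(5/624) = 0.99. The standard error of its logarithm is √(1/5 − 1/630 + 1/5 − 1/624) = 0.63, so the 95% CI is 0.29 to 3.40.

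**Step 6: would a test show it?** Usually not. Fisher's exact test gives p = 0.13 for 8/20 against 8/40, p = 0.08 for 10/20 against 10/40, and p = 0.22 for 5/10 against 5/21. The shift would look large in a table without being significant.

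**The case against.** The strongest reply is that the article names a secondary topic and no more. It states no between-arm test of stage, and tabulation is commonly left to a fuller document. Anyone with stage counts by arm and the arm sizes can work out the rate per woman. Section 2.8 claims only preliminary information and disclaims early efficacy effects, and excess cancers are a separate endpoint. The proposed rate would itself be very imprecise.

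Much of this stands, and it limits the point to one of interpretation. Four stronger readings are tempting but unsupported:
- *The plan tests stage between arms.* None is stated; the endpoint is descriptive.
- *Stage covers screen-detected cancers only.* Section 2.7 refers to invasive cancers and section 2.8 to incident cancers. Section 2.6 speaks of detected cancers, but as a data field, so interval and later cancers may be included.
- *Histology has the same defect.* It is not defined as a distribution. Its case mix is affected by the same denominator, but the stage-shift argument does not carry over directly.
- *The stage result will drive the efficacy trial's design.* Section 2.8 sizes that trial on deaths or metastatic cancers and does not name stage as an input.

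Three parts of the reply do not remove the concern. The form of the endpoint, a distribution among cases, is stated and not merely left open. Limiting it to invasive cancers does not help, because the 2:1 split is itself stated for invasive cancers. And the disclaimer about too few cases concerns metastatic or locally advanced disease, while the stage distribution as a whole is presented as informative.

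**Conclusion.** The concern holds as a risk of misreading one descriptive secondary endpoint. The primary analysis is not affected. Under the plan's own 1:2 split with 1:1 allocation, the later-stage share among cases can fall by up to half with no fewer later-stage cancers and a rate ratio of about 1.0 per woman randomised.

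This rests on three assumptions: a control share of 20% to 50%, which is not from the document; equal later-stage counts in the two arms, chosen to represent no benefit; and persistence of the 2:1 ratio, which the plan expects over 5 years but which catch-up would weaken. A reader might infer that any observed stage shift must be artefact. The documents do not support that either: MRI may truly reduce later-stage disease, and a distribution among cases cannot separate the two explanations.

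**What to change.** - Report, by arm, the cumulative number of invasive cancers in each stage group per woman randomised, with a confidence interval. Stage II or higher and node-positive are examples of suitable groups; the article defines none, so the sponsor should fix them before looking at results by arm.
- Count screen-detected, interval and later cancers over the full planned clinical follow-up of at least 5 years.
- Confirm that stage is recorded for interval and later cancers, since section 2.6 mentions only detected ones.
- Keep the stage distribution among cases as description only, with a sentence of caution on length bias and overdiagnosis. A similar caution would suit the histology table.

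The cost is a change of endpoint wording and, if stage of interval and later cancers is not already captured, some extra data collection. The result will be less striking and the interval wide, on the order of 0.29 to 3.40 in the illustration above. That width is an honest statement of what a trial of this size can say.

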## 3. Characteristics of Enrolled Patients

From July 2013 to November 2015, a total of 1254 women (mean age 47.2 ± 4.6 years) were enrolled: 624 were assigned to MX plus US (standard of care arm) and 630 to MRI (experimental arm). Table 2 reports the number of women recruited in each center, and their characteristics are detailed in Table 3.

Most women were below the age of 50 (72.2%) and premenopausal (44.6%) or perimenopausal (23.7%). More than one in four (27.6%) did not have children; 52.1% used oral contraceptives (currently or in the past); 15% of postmenopausal women had used HRT. Most women (86.3%) had a body mass index <25. Only 4.6% of enrolled women (58/1254) had their first breast examination in this trial, and most of them (44/58) were in their forties. Among women with a previous MX, an extremely dense breast at the most recent MX was recorded for 82.7% (984/1196). Breast and/or ovarian cancer in mothers and/or sisters was reported by 36.5% of enrolled women (458/1254) and 67 of them had a BC-LTR < 15%. A BC-LTR ranging from 15% to 30% was calculated for 41% (514/1254) of all enrolled patients, and 47.5% of them (244/514) also had a previous MX classified as extremely dense. Overall, 59% of enrolled women (740/1254) had, as a sole inclusion criterion, an extremely dense breast at MX (LTR < 15% and BD = *d*).

The distribution of major determinants of breast cancer risk profiles of women enrolled in the study varied across centers: the rate of women recruited on the basis of an MX classified as extremely dense ranged from 0% to 98.9% (Table 4).

The frequency of women reporting one or more first-degree relatives affected by breast and/or ovarian cancer ranged from 26.6% to 91.7%.

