
## 5. Conclusions

The rationale of the MRIB trial stems from the general need to acquire a more accurate understanding of the costs and benefits associated with the extension of MRI screening outside the high-risk setting. While other large-scale studies such as the DENSE trial [24] explored the use of MRI in the screening setting as a supplemental examination, the MRIB trial compares MRI alone to MX+US, in an effort to balance diagnostic performance, risk-effectiveness, and cost-effectiveness. Pioneering the stand-alone use of MRI in the intermediate-risk setting, this trial has a feasibility design that, despite the main limitations of its preliminary nature and of the inability to reach the expected recruitment, will allow us to provide useful information on the acceptability of the two screening models and on their diagnostic performance in terms of second-look examinations, short-term reevaluation, invasive procedures, and diagnostic yield. Furthermore, data from the planned 5-year follow-up should allow the estimation of the magnitude of overdiagnosis, if any, associated with MRI. In a broader timeframe, the MRIB trial will also contribute data for the informed performance of cost–benefit analyses and, potentially, for the design and planning of a formal head-to-head efficacy trial of MRI screening in women at intermediate breast cancer risk.

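### Secondary endpoint 6 calls the whole excess of MRI-arm cancers overdiagnosis: at best an upper bound, with an unsettled horizon, and not estimable with useful precision from 1254 women

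*Protocol article*

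**What the plan says.** Section 2.7 lists, as secondary endpoint 6, invasive and in situ cancers "detected in excess in the experimental arm compared to the conventional arm (overdiagnosis) after 4 years of follow up". The bracketed word makes the whole excess overdiagnosis.

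Section 5 states that "data from the planned 5-year follow-up should allow the estimation of the magnitude of overdiagnosis, if any, associated with MRI". Section 2.8 says that "A clinical follow-up of all randomized women is planned for at least 5 years", and the Abstract describes "the primary endpoint being the rate of cancers detected in the 2 arms after 5 years of follow-up". Neither Section 2.7 nor Section 5 says whether the years run from randomization or from the second round.

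On the design, Section 2.1 says "Two screening rounds per woman were planned", at yearly intervals and "with a 1:1 allocation ratio". Section 2.5 sends women with negative findings back to "usual screening if the two study rounds had been completed". Section 3 reports the numbers reached: "624 were assigned to MX plus US (standard of care arm) and 630 to MRI (experimental arm".

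Section 2.8 also predicts that invasive cancers over 5 years will divide one to two between control and MRI. It reads this as confirming doubled sensitivity and as preliminary information on lead time.

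**The concern.** A more sensitive test finds some cancers earlier. Until those cancers have had time to appear in the comparison arm, the count in the MRI arm is higher even if no woman is overdiagnosed. Section 2.8 accepts this mechanism; endpoint 6 makes no allowance for it. Followed as written, the endpoint would report residual lead time as harm from MRI.

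Two further matters bear on the result. The excess shrinks as the control arm catches up, so the horizon and its origin affect the answer, and the article does not settle them. Section 5 also promises a magnitude directly after conceding that recruitment fell short, with no statement of precision. The article intends the trial to inform cost–benefit analyses and a later efficacy trial. An excess due to lead time could be carried forward as overdiagnosis, or a wide null result could be read as reassurance.

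**Working it through.** **Inputs from the article.** 1254 women, so 627 per arm on average (Section 3). Average ten-year risk 5%, lowest about 3% (Section 2.8), taken as constant at 0.5% and 0.3% per year. Two annual rounds (Section 2.1), so study screens at about years 0 and 1. Twofold sensitivity of MRI (Section 2.8 and Discussion).

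**Assumptions not in the article.** Exponential preclinical phase with mean m of 2 to 4 years; sensitivities of 0.90 for MRI and 0.45 for control (ratio of two); no overdiagnosis; clock from randomization.

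**1. The article's own count.** 2000 × 0.005 × 5 = 50 cancers, inside its stated 40–60. Split one to two, 40 becomes 13.3 and 26.7 (excess 13.3), and 60 becomes 20 and 40 (excess 20). Section 2.8 reads such an excess as sensitivity and lead time; Section 2.7 gives an excess of the same kind the name overdiagnosis.

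**2. Catch-up time.** From randomization, 4 years leaves 4 − 1 = 3 years after the last study MRI, and 5 years leaves 4. If the 4 years run from the second round, they end at 1 + 4 = 5 years from randomization.

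**3. Residual lead time with no overdiagnosis.** In units of the yearly incidence, cumulative cancers by year T are T + A(s), where A(s) counts cancers found at a study screen that would otherwise have surfaced after T:

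A(s) = s·m·[exp(−T/m) + (1 − s·exp(−1/m))·exp(−(T−1)/m)]

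The ratio of arms is [T + A(0.90)] / [T + A(0.45)].

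| T | m | A(0.90) | A(0.45) | Ratio |
|---|---|---|---|---|
| 4 | 2 | 0.426 | 0.268 | 4.426/4.268 = 1.04 |
| 4 | 4 | 1.833 | 1.215 | 5.833/5.215 = 1.12 |
| 5 | 2 | 0.258 | 0.162 | 5.258/5.162 = 1.02 |
| 5 | 4 | 1.428 | 0.946 | 6.428/5.946 = 1.08 |

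These rows have no screening after year 1. Adding annual screens from year 2 at sensitivity 0.40 in both arms, as one version of the return to usual screening, lowers the ratio to 1.01–1.04 at 4 years and 1.00–1.01 at 5. Across both settings the residual is about 1–12% at 4 years and 0–8% at 5.

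**4. Precision when the true ratio is 1.** Expected cancers per arm d = n × yearly risk × years; SE of the log ratio = √(2/d); 95% interval = exp(±1.96 × SE).

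| n per arm | Yearly risk | Years | d | SE | 95% interval |
|---|---|---|---|---|---|
| 627 | 0.005 | 4 | 12.5 | 0.40 | 0.46–2.19 |
| 627 | 0.005 | 5 | 15.7 | 0.36 | 0.50–2.01 |
| 627 | 0.003 | 5 | 9.4 | 0.46 | 0.41–2.47 |
| 1000 | 0.005 | 4 | 20 | 0.32 | 0.54–1.86 |
| 1000 | 0.005 | 5 | 25 | 0.28 | 0.57–1.74 |

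At 0.5% per year, a two-proportion comparison of 624 with 630 women has about 7% power at 4 years and 8% at 5 for a true 20% excess.

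**The case against.** The strongest reply is that this is a secondary endpoint of a declared feasibility study with no power claim for overdiagnosis. Section 5 is hedged and admits the missed recruitment in the sentence before. That stands, and it limits the severity. It does not rescue the label in Section 2.7.

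Four stronger readings are tempting, and the documents do not support them.

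- *The 4 and 5 years contradict each other.* A reader might infer this. But a 4-year readout fits inside follow-up of at least 5 years, and 4 years from the second round is about 5 from randomization. The fault is an unstated origin that leaves two horizons unreconciled.
- *The lead-time residual is large, perhaps more than a third.* The article gives no lead-time figure. In the model above, ratios that high need an essentially unscreened control arm: with A = 0 for control, m = 4 and T = 4, the ratio is 5.833/4 = 1.46. Sections 2.1 and 2.5 rule that out, since the control arm has annual mammography plus ultrasound and then usual screening. A longer phase detectable only by MRI would raise the residual, but nothing in the article quantifies it.
- *The magnitude cannot be estimated at all, because of the shortfall.* A point estimate is possible. What is lacking is useful precision, and 2000 women would not have supplied it either.
- *The article's own excess of 13–20 cancers is what endpoint 6 would mislabel.* That forecast concerns invasive cancers over 5 years in 2000 women; endpoint 6 also counts in situ disease and stops at 4 years. The two share a mechanism, not a number.

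It is also fair to say that moving from 4 to 5 years helps only modestly, and that a changed horizon would have to be disclosed. The fix below therefore keeps both.

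**Conclusion.** The point holds in limited form and should be fixed. Endpoint 6 is wrong as worded: the excess is in expectation overdiagnosis plus residual lead time, so it is biased upward as a measure of overdiagnosis and is at best an upper bound. The direction follows from the design and from Section 2.8's own account. The size (about 1–12% at 4 years, 0–8% at 5) rests on the assumed twofold sensitivity and 2–4-year mean preclinical phase, and lies towards the low end if usual screening continues.

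The claim in Section 5 is not supported with useful precision. At the article's average risk the interval around no excess runs from roughly a halving to a doubling at either horizon, far wider than the lead-time residual. In situ cases beyond the assumed risk would add events, but even 25 cancers per arm leave 0.57–1.74.

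**What to change.** - **Section 2.7.** Name endpoint 6 *cumulative excess incidence (upper bound for overdiagnosis)*. State randomization as the time origin. Report cumulative incidence by arm at the stated 4 years and at the planned 5 years, and disclose any change to the prespecified horizon.
- **Sections 2.7, 2.8 and 5.** Reconcile the horizons. If 4 years was always meant from the second round, say so.
- **Section 5.** Replace the capability claim with a descriptive estimate and its expected interval, for example a ratio interval of about 0.50–2.01 at 5 years under 5% ten-year risk and 0.41–2.47 under 3%.

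No new data or visits are needed, because at least 5 years of follow-up is already planned. The cost is a less favourable statement of what the trial can show about overdiagnosis, plus the disclosure if the horizon is altered.
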